**Fig. 3 Fig3:**
[figure not shown]
Study schema

The randomized fast-track trial (with delayed assignment to NCSG for both comparison groups) is seen as a more acceptable design to patients, families and staff, given that the majority of eligible participants will have a strong preference for assignment to the NCSG group. Moreover, we feel this design, which was used in the pilot study, will optimize recruitment and retention of the comparison group participants in the trial.

The follow-up period after the intervention (weeks 13 to 24) will follow a longitudinal observational design and provides an opportunity to examine factors related long-term adherence to night-time compression.

### Participants

The following eligibility criteria will be used to determine participant inclusion in the trial:Women with a histological diagnosis of breast cancer experiencing lymphedema in the ipsilateral arm such that there is a minimum 200 ml or 10 %, and maximum 40 % increase in arm volume over the unaffected arm (indicative of mild to moderate lymphedema) [14].Survivors must have completed all primary and adjuvant cancer treatments (with the exception of hormonal treatment) by a minimum of 1 month prior to randomization.Survivors must be in or entering the lymphedema maintenance phase and agreeable to **not** pursuing any other lymphedema maintenance treatments beyond day-time use of a compression sleeve.Survivors must have their own properly fitted compression sleeve for day-time maintenance and must agree to wear their day-time sleeve as per standard care for a minimum of 12 h per day.No current use of night-time compression for maintenance. Any survivor who has trialed a NCSG/performed night-time CB in the past year for maintenance purposes must observe a one-month washout period before entering the trial.

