At present, there are no known curative treatments, either surgical or pharmacological, for lymphedema [9]. Rehabilitative treatments, also called conservative treatments, are prescribed to reduce and maintain limb size, to restore function, to reduce pain, and to improve the appearance of the limb [9, 10]. An initial intensive treatment program is usually prescribed to reduce the lymphedema (Phase I) and is followed by a maintenance phase (Phase II) which aims to promote life-long maintenance [11]. Decongestive Lymphatic Therapy (DLT) is a 2-to-4 week intensive treatment program comprised of daily manual lymph drainage (MLD) massage (a specialized massage technique), wrapping with multi-layered short-stretch compression bandages (worn 23 h per day), exercise, and education [12]. The current recommended intensive treatment approach for Phase I is DLT, with or without the inclusion of the MLD massage component [9]. Following treatment to reduce the swelling, a compression sleeve is prescribed. Compression sleeves represent current standard of care in lymphedema maintenance (Phase II) [9].

A prospective cohort study including 682 women with breast cancer related lymphedema examined the ability of women to maintain arm lymphedema volume following an intensive course of reduction treatment for lymphedema [13]. In the study, the authors observed a gradual increase in lymphedema volume over time among study participants, with the greatest increases seen in the first year. The risk of treatment failure, defined as a >50 % relapse in arm lymphedema volume from baseline levels, was 38.1 %, 53.1 %, and 64.8 % at 1, 2, and 4 years respectively [13]. Interestingly, women who wore a day-time compression sleeve and also wrapped their affected limbs with compression bandages (CB) at night (a minimum of 4 nights per week), had a significantly reduced risk of relapse in arm lymphedema volume [hazard ratio, 0.53, (0.34–0.82), *P* = 0.004] [13]. The authors concluded that successful control of lymphedema may be dependent on the combined use of the compression sleeve and CB during day and night periods, respectively.

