### Objectives

The primary objectives of the randomized controlled phase of the trial are to determine the effect of night-time compression on arm lymphedema volume maintenance and quality of life in breast cancer survivors who have completed intensive reduction treatment for their lymphedema. These questions are seen as valuable for informing implementation of night-time compression as a self-management strategy for lymphedema in the clinical setting. The primary objectives of follow-up are to evaluate the long-term adherence to use of night-time compression and the timing of the intervention effect. As well, this follow-up period will allow us to better understand who may benefit the most (or least) from the addition of night-time compression.

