### Statistical analyses

Baseline medical and demographic characteristics, arm dominance relative to the lymphadematous arm, and adverse events of the three groups will be compared using one-way ANOVA for continuous data and Pearson’s Chi-square tests for categorical data. The primary analysis will compare the groups with regard to percent excess lymphedema volume and quality of life at 12-weeks using a one-way ANOVA. General linear models will be used to adjust for centre and lymphedema category (mild or moderate), and to evaluate the treatment effect in subgroups defined by the strata. Sleep quality, self-efficacy, and adherence-related outcomes will be analyzed by repeated measures modeling and one-way ANOVA on change scores.

Descriptive data on accrual rates will include the number of women screened for eligibility, the number eligible, the number agreeing to participate, and reasons for refusal to participate. Data on adherence will be collected from all women throughout the 24-week study period. Adherence data will include days worn per week and hours worn per 24-h period, as appropriate, for each of the following: 1) NCSG; 2) CB; 3) day-time compression sleeve. We will also examine adherence during weeks 13 to 24 to the newly assigned NCSG for the standard care and standard care + CB groups, and ongoing adherence during weeks 13 to 24 in the originally assigned standard care + NCSG group. Analyses of primary outcomes will be performed at the end of the RCT portion of the trial. Within group analyses will also be conducted for primary and secondary outcomes from weeks 13 to 24 following completion of all follow-up measures.

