### Limitations

Limitations of the current design include the requirement that participants be able and willing to be randomized to one of the three groups for a 12-week period. For this reason, we anticipate women who regularly administer CB at night and/or attend regular maintenance sessions of MLD will not be interested, or eligible to take part in the trial.

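### Time since intensive reduction is probably prognostic for week-12 arm volume, yet it is not named for stratification, adjustment or subgroups

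*Protocol article*

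**What the plan says.** Under Participants, the protocol article opens the trial to two kinds of woman: "Survivors must be in or entering the lymphedema maintenance phase". No minimum or maximum time since the end of reduction treatment is given. Two further criteria deal with earlier night-time compression. One reads "No current use of night-time compression for maintenance". The other applies to a woman who has tried a night-time garment or bandaged at night "in the past year for maintenance purposes must observe a one-month washout period before entering the trial". Both are tied to maintenance use.

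The Background describes the phase before maintenance as including "wrapping with multi-layered short-stretch compression bandages (worn 23 h per day", which takes in the night. It then cites a cohort of 682 women in which volume rose gradually after reduction, with the largest increases in the first year. In that cohort the risk of a relapse above 50 % "was 38.1 %, 53.1 %, and 64.8 % at 1, 2, and 4 years respectively".

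Methods/Design names two stratification factors, centre and severity (mild or moderate). Statistical analyses makes a one-way ANOVA at week 12 the primary comparison. It adds general linear models that adjust for the same two factors and are used "to evaluate the treatment effect in subgroups defined by the strata". Under Objectives, the follow-up period is meant to help the investigators "better understand who may benefit the most (or least) from the addition of night-time compression".

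**The concern.** A woman who finished reduction treatment last week and a woman several years into maintenance can both be randomized. By the protocol's own account of the natural course, the first is at the start of the period of fastest volume increase and the second is well past it. Their expected week-12 volumes probably differ whichever arm they are in.

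A factor of that kind matters in three ways when it is left out of the analysis. It adds between-woman variation that a covariate could remove. It can fall unevenly across arms of 40 by chance. And the average effect is harder to interpret when a reader cannot tell how far it comes from newly reduced women and how far from established ones. The subgroups that are named, centre and severity, do not speak to that last question.

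**Working it through.** **1. The plan's own figure.** Sample size gives 36 per group, a difference of 20 %, SD 25, alpha 0.05 and 86 % power by one-way ANOVA. With means 0, 10 and 20, the noncentrality is 36 × (10² + 0² + 10²) / 25² = 11.52, and the noncentral F distribution with 2 and 105 degrees of freedom gives 85.9 %. The stated power reproduces, and nothing below makes it wrong.

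**2. Does the document itself point to a time gradient?** From the cohort relapse risks in the Background, with a constant hazard within each interval:

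- Year 1: −ln(0.619) = 0.480 per year
- Year 2: ln(0.619/0.469) = 0.278 per year
- Years 3 and 4: ln(0.469/0.352)/2 = 0.143 per year

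The ratio of first to last is 0.480/0.143, about 3.3. Over 12 weeks, 1 − exp(−h × 12/52.18) gives 10.4 %, 6.2 % and 3.2 %. These are risks of relapse above 50 %, not values of percent excess volume. They support the direction of a prognostic gradient and give no effect on the trial's endpoint.

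**3. What unadjusted pooling could cost.** The documents give neither the share p of newly reduced women nor the difference D between the two groups in week-12 volume. Both are assumptions here. If 25 is the SD within each group, the pooled SD is √(25² + p(1−p)D²).

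| p | D | Pooled SD | ANOVA power |
|---|---|---|---|
| – | 0 | 25.0 | 85.9 % |
| 0.25 | 10 | 25.4 | 84.8 % |
| 0.25 | 20 | 26.5 | 81.5 % |
| 0.25 | 30 | 28.2 | 76.1 % |
| 0.50 | 10 | 25.5 | 84.4 % |
| 0.50 | 20 | 26.9 | 80.1 % |
| 0.50 | 30 | 29.2 | 73.1 % |

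If 25 already includes this variation, the plan loses nothing against its stated power, and adjustment is a gain instead. At p = 0.5 and D = 20, the SD falls to √(625 − 100) = 22.9.

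**4. Chance imbalance.** For two arms of 40, the SE of the difference in the newly reduced share is √(2p(1−p)/40). This is 0.102 at p = 0.3 and 0.112 at p = 0.5, so the 95 % range is about ±20 to ±22 percentage points. A gap of 0.22 with D = 20 would move the between-arm difference by 0.22 × 20 = 4.4 points. The SE of that difference is 25 × √(2/40) = 5.6, and the planned difference is 20.

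**The case against.** The strongest reply is that mixed time since reduction is ordinary case mix. The Objectives define the population as women who have completed intensive reduction treatment, and the Background calls the day-time sleeve current standard of care in maintenance. Enrolling both groups is therefore deliberate, and randomization protects the comparison. All of this stands. Chance imbalance is also already reflected in the standard error and in alpha. On the relapse scale, even a gap of 20 to 22 points in mix times the 7.2-point risk difference (10.4 − 3.2) shifts a between-arm comparison by only about 1.4 to 1.6 points.

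The cohort figures are weak evidence of size. A falling hazard may partly reflect early loss of relapse-prone women rather than time itself. The article is also condensed: a full protocol or analysis plan may hold further covariates, and Statistical analyses does not say that centre and severity are the only ones. The aim of learning who benefits belongs to the observational follow-up, so it does not oblige a week-12 subgroup.

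These points limit the finding without removing it. The article does name its stratification factors, adjustment factors and subgroups, and the variable its own Background singles out is not among them.

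**Conclusion.** The point holds as an inexpensive improvement to the analysis, not as an error. Time since reduction is likely to be prognostic for week-12 volume, and the article makes no named use of it. The consequence is lost precision, exposure to chance imbalance and a less interpretable average effect. No volume figure can be derived from the documents. The power range of 73 % to 85 % rests on assumed shares of 25 or 50 %, assumed shifts of 10 to 30 points, and a planning SD that does not already contain the variation.

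A reader might infer more, and the documents do not support it:

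- **That the comparison is biased.** Allocation is random, so the mix is balanced on average.
- **That standard care withdraws night compression which the other arms continue.** Intensive bandaging ends for every entrant, because that phase is complete. Both night-time arms start with a 2-week phase-in, and the garment arm also waits for delivery.
- **That the washout removes a small carry-over and leaves a larger one.** No section quantifies carry-over from any of these treatments.
- **That Participants and Limitations conflict over manual lymph drainage.** Participants requires women to forgo other maintenance treatments. Limitations expects that women who regularly bandage at night or "attend regular maintenance sessions of MLD will not be interested, or eligible" to take part. The two agree.
- **That the washout should be changed.** Extending it would delay or exclude women whom the criteria deliberately admit. Only its intended scope is unclear.

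**What to change.** - Record at the baseline visit the date on which the last intensive reduction course ended. For women already randomized (39 by September 2015), the date may be obtainable from the medical records that are abstracted anyway.
- Pre-specify time since reduction, or newly reduced versus established maintenance, as a covariate in the general linear models, beside centre and severity. The gain in precision appears in those models and not in the unadjusted ANOVA.
- Report one exploratory treatment-by-time-since-reduction comparison at week 12, labelled as support for the aim of learning who benefits most or least.
- State whether the washout is meant to cover intensive-phase bandaging. The sponsor decides this, and no change of rule is proposed here.

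The cost is one data field, one model term, one exploratory comparison and a clarifying sentence. With 120 women in three arms the subgroup estimate will be imprecise, so it can help interpretation but cannot carry a separate claim.

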### Survivors will be excluded if they present with any of the following

Clinical or radiological evidence of active breast cancer, either local or metastatic.History and clinical diagnosis of bilateral arm lymphedema.Serious non-malignant disease, such as renal or cardiac failure, which would preclude daily treatment and follow-up.Survivors for whom compression is contraindicated, such as those with untreated infections, skin irritation/rash or thromboses in the affected arm.Psychiatric or addictive disorders, as determined by the referring physician, which preclude obtaining informed consent or adherence to the protocol.Unable to comply with the protocol, measurement, and follow-up schedule due to factors, such as vacation during the study period.

### Interventions

Management in both the experimental and comparison groups will follow recommendations of the Canadian Breast Cancer Initiative’s Steering Committee for Clinical Practice Guidelines for the Care and Treatment of Breast Cancer [15]. Survivors will be provided with advice concerning good skin care, regular exercise, maintenance of a healthy body weight, and the use of a day-time compression sleeve.

#### Group 1: standard care: day-time use of compression sleeve alone

Women randomized to the standard care group will receive standard care for lymphedema maintenance. In this group of the trial, each participant will be instructed to wear their day-time compression sleeve with or without a gauntlet/glove (worn if swelling in the hand and fingers), providing a minimum of 30 mm Hg of pressure, for 12 h per day, each day of the week. A 6-week follow-up will be performed to evaluate response and adherence to the standard care protocol. At week 12, women in this arm of the trial will be fitted for a NCSG and will follow the protocol outlined in the experimental arm of the trial.

#### Group 2: standard care plus night-time multi-layered Compression Bandaging (CB group)

Women randomized to the night-time CB group will be instructed in the application of night-time multi-layered CB by the physical therapist. Women who have performed nighttime multi-layered CB as part of their past maintenance program will attend a review session to ensure appropriate bandaging technique and application. Educational materials related to compression bandaging application will be provided. Participants will have a 2-week phase in period, following which they will be asked to wear the CB at night while sleeping for a minimum of 8 h per night, a minimum of five nights per week for 4 weeks (weeks 3–6). As per standard of care, each participant will be required to wear their day-time compression sleeve with or without a gauntlet/glove, providing a minimum of 30 mm Hg of pressure, for 12 h per day, each day of the week. A 6-week follow-up will be performed to evaluate response and adherence to the CB protocol. At that point, maintenance CB a minimum of 3 times per week will be introduced. At week 12, women in this arm of the trial will be fitted for a NCSG and will follow the protocol outlined in the experimental arm of the trial.

#### Group 3: standard care plus Night-Time Compression System Garment (NCSG group)

Women randomized to the immediate NCSG group will be measured for a NCSG. Once the garment has arrived, participants in this group will be instructed in use of their NCSG by the physical therapist. Educational materials related to garment application and maintenance will be provided. Participants will have a 2-week phase in period, following which they will be asked to wear the NCSG at night while sleeping for a minimum of 8 h per night, a minimum of five nights per week for 4 weeks (weeks 3–6). As per standard of care, each participant will be required to wear their day-time compression sleeve with or without a glove/gauntlet, providing a minimum of 30 mm Hg of pressure, for 12 h per day, each day of the week. A 6-week follow-up will be performed to evaluate response, adherence to the protocol and to address any issues with wear of the NCSG. At that point, maintenance NCSG a minimum of 3 nights per week will be introduced. After the 12-week assessment, participants in this arm of the trial will have the option to continue use of their NCSG.

### Recruitment

Ethics approval and signed informed consent of participants is required. Recruitment started after approval was received from all respective Health Research Ethics Committees (Health Research Ethics Board of Alberta: Cancer Committee and the University of British Columbia Ethics Board). The estimated timeline for recruitment is 18–24 months. Potential participants will be identified and screened for eligibility by the respective research coordinators through the Rehabilitation Medicine Departments at the CCI in Edmonton, the TBCC in Calgary, and MSJ in Vancouver. Initial eligibility will be determined by chart review and, if necessary, verified through contact with the participant’s physician. Interested participants will be scheduled for a baseline visit to obtain written consent and for final determination of eligibility. It is anticipated that 10 to 15 breast cancer survivors with lymphedema (per month) will be eligible among the three centres and that 5–8 women (per month) will agree to participate. Follow-up measurements will occur at week 6, 12 (end of RCT portion), 18, and 24 following the start of the assigned intervention for the participant. The last participant entering the trial will therefore undergo her 24-week follow-up measurement approximately 30 months after recruitment begins.

### Baseline data and endpoints

During the baseline visit, demographic and clinical information will be collected on participants. Medical data will be abstracted from the medical health records.

### Primary endpoints

*Arm volume* is a commonly used metric to evaluate lymphedema severity and to inform decision-making in the clinical setting. Lymphedema will be objectively measured using the Perometer (Pero-systems, Wipputal, Germany). The Perometer is an optoelectric limb volumeter that uses infrared technology to quantify limb volume and determine inter-limb difference. Measurement with the perometer takes approximately 3 min to complete. The perometer is a valid, reliable, and sensitive method for quantifying limb volume [16–18].

*Quality of life* will be measured using the condition-specific Lymphoedema Functioning, Disability and Health Questionnaire (Lymph-ICF) [19]. This 29-item questionnaire was developed to assess quality of life specific to lymphedema and to monitor progress of treatment on function (i.e., movement, activities) and symptoms related to lymphedema (i.e., pain, discomfort, heaviness, and tension) as well as to assess activity limitations and participation restrictions. The Lymph-ICF has been tested and shown to be valid and reliable [19]. As well, general health-related quality of life will be assessed at each visit by using the RAND 36-item Short Form Health Survey (SF-36). These two questionnaires will take approximately 10–15 min to complete.

### Secondary endpoints

Secondary endpoints will include bioimpedance analysis, adherence, sleep disturbance, and self-efficacy.

*Bioimpedance analysis* (BIA) will be used to assess *extracellular fluid status* within the arm. BIA measures the impedance of flow from a low alternating electrical current that is applied to the body through a skin electrode. BIA records impedance values for each limb and provides an index that correlates with quantitative measurements of volume increase in limb size seen in the arm with lymphedema [20]. BIA is a simple, painless procedure that takes less than 5 min to perform. BIA has been shown to be a more sensitive measure than arm volume in detecting changes in lymphedema in those with **early mild lymphedema** but less reliable in those with long-standing lymphedema [20]. This measurement will provide information on extracellular fluid changes that complements the data on arm lymphedema volume.

*Sleep disturbance* will be assessed using the RAND Medical Outcomes Survey Sleep Survey [21]. The survey measures 6 key dimensions of sleep: sleep initiation, maintenance, quantity, adequacy, drowsiness, and respiratory impairments (e.g. shortness of breath, snoring). The sleep scale will be used to assess the impact, if any, of wearing night-time compression on sleep quality. The questionnaire takes 5 min to complete.

#### Self-efficacy of lymphedema management

Self-efficacy will be assessed based on the 6-item Chronic Disease Self-Management scale [22] modified for use with lymphedema. The scale assesses several domains that are common across chronic diseases such as symptom control, role function, emotional functioning, and communicating with physicians. The questionnaire takes 3-to-5 min to complete.

*Body height* will be recorded at baseline and *body weight* at baseline and each follow-up time point.

